***iv) Preliminary evidence of AP-induced disruptions in central insulin sensing in rodents***

Based on our well established rodent model demonstrating that OLA can acutely induce hepatic insulin resistance, we set out to explore whether this could be occurring via defective insulin sensing at the level of the brain. We used healthy rats (avoiding confounding effects of illness) which were given an acute injection of OLA (to avoid adiposity changes). In our previous work, we had employed hyperinsulinemic euglycemic clamps (HIEC) (15, 38), which we elected to avoid in the present paradigm. The HIEC involves a high dose of intravenously infused insulin which continuously reaches the brain (while glucose levels are kept constant at fasting levels). Thus insulin effects are *not* limited to the brain (and stimulate most tissues in the body), making dissection of peripheral and central effects difficult. Here we used the so called “pancreatic euglycemic clamp procedure” to assess glucose metabolism. During a pancreatic clamp, a peripheral infusion of somatostatin blocks endogenous production of insulin, which is then replaced at “basal” levels *via* a peripheral insulin infusion. Replacement of insulin within physiological “basal” levels allows separate manipulation of central insulin concentrations via an ICV infusion. A central insulin infusion, provided there is no leakage into the circulation, isolates central from peripheral insulin effects. During the pancreatic clamp an exogenous infusion of glucose is adjusted to maintain euglycemia in the animal. The amount of glucose an animal requires to maintain euglycemia (glucose infusion rate), is a measure of whole body insulin sensitivity. A tracer infusion allows for separate determination of glucose production and glucose utilization. Under these conditions, with no evidence of ICV insulin leakage into the periphery, we found that OLA acutely blocked the ability of central insulin to suppress endogenous glucose production by the liver (with *no effect* on glucose disposal), providing, for the first time, evidence that OLA impairs central insulin action, independently of changes in adiposity. Another interesting observation was that there was no effect of OLA on glucose production in the absence of a central insulin stimulus during clamp conditions. (See **Figure 3**, *manuscript in preparation*).

[figure not shown]

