On **Day 1**, participants will be admitted to the Centre for Addiction and Mental Health (CAMH) (to our reserved research bed) or at a nearby hotel if beds are not available, provided a standardized mixed meal at around 5 P.M, (The meal can be eaten by the participant at any time up until 7:00 pm, to allow a period of at least 12 hours of fasting prior to clamp initiation the following morning). This meal will be followed by a fast and overnight stay. OLA 7.5 mg (or placebo) will be taken by the participant at bedtime. The participants will be admitted to ensure participant availability early in the morning for the clamp and tests, and to provide a standardized milieu before the test. Per PI discretion, the participant may have the option of staying at home on this night (for example, if the participant is not comfortable staying at a hotel such as due to due covid-related concerns, and they live within a reasonable distance where they can be picked up by a taxi in the morning).

On ***Day 2***, at 6AM, they will be transported to the Toronto General Hospital (TGH):

- At approximately 7AM (7-9AM) (t=-120 minutes), the pancreatic euglycemic clamp (total duration 480 minutes) will be initiated. Glucose production is quantified via a primed constant infusion of D2-glucose (dextrose infusion) (22.5 mmol/kg bolus followed by 0.25 mmol/kg/min) administered for the duration of the clamps.
- To maintain “pancreatic clamp” conditions, an IV infusion of somatostatin (30µg/hour) is initiated at t= -120 min (i.e. 7AM) to inhibit insulin, glucagon and growth hormone secretion, and concurrently replaced by a basal rate infusion of these hormones: insulin (Humulin R, Eli Lilly Canada) at 0.05units/kg/min; human recombinant growth hormone (Humatrope, Eli Lilly Canada) at 3ng/kg/min; and glucagon (Eli Lilly Canada) at 0.325ng/kg/min.
- A 20% dextrose solution, is administered as necessary to maintain euglycemia (where infusion rate represents a measure of whole body insulin sensitivity).
- At t=0 (i.e. 9AM), the participants receive 40 IU of intranasal insulin (INI) lispro, a dose which has previously been shown to suppress endogenous glucose production (by 35% relative to placebo (PL)) ^23^, or intranasal placebo (INP) via a metered nasal dispenser.

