- As per established protocol, because of some spillover of 40 IU of INI lispro, volunteers during the INP visit will receive an IV infusion of insulin lispro 0.005IU/kg (or the diluent equivalent during an INI visit) over 30 minutes starting at the same time as intranasal administration.
- OLA (10mg) or PL is also administered at t=0, with timing of OLA based on pharmacokinetics, and peak plasma levels occurring within 4-6 hours, and on our single dose protocol in healthy volunteers demonstrating acute changes in glucose metabolism^18^.
- Blood samples are drawn every 30 min after the start of the clamp (t=-120 min to t=0 min), and every 10 minutes after intranasal insulin administration (t=0 to t= 360 min). The total amount of blood taken will be approximately 250 ml over the course of 6 hours.
- Blood is centrifuged immediately, and plasma stored at -20 C for further analysis. For long-term storage (later analysis), plasma will be stored at -80 C.
- OLA levels, free fatty acids, triglycerides, insulin, c-peptide, glucagon, GLP-1 and catecholamines will be measured via the central laboratory of TGH.
- The clamp procedure ends at 3pm (t=360 min), and participants are provided food, monitored for the remainder of the day (i.e. monitoring for blood pressure and sleepiness for a minimum of 30 min post-clamp) and sent home on the evening of ***Day 2***.

***
[figure not shown]

[figure not shown]
***

1. ***Cognitive Testing and MRI*** (**Days 0-2*) (*Figure 5*)*:**

On **Day 0**, participants will take OLA 5 mg (or placebo) at their home.

On **Day 1**, participants will be admitted to the Centre for Addiction and Mental Health (CAMH) (to our reserved research bed) or at a nearby hotel if beds are not available, provided a standardized mixed meal at around 5 P.M followed by OLA 10 mg (or placebo). The meal can be eaten by the participant at any time up until 9:00 pm. This meal will be followed by a fast and overnight stay. The participants will be admitted to ensure participant availability in the morning for the blood and cognitive tests, and to provide a standardized milieu before the tests. Per PI discretion, the participant may have the option of staying at home on this night (for example, if the participant is not comfortable staying at a hotel such as due to due covid-related concerns, and they live within a reasonable distance where they can be picked up by a taxi in the morning).

On ***Day 2:***

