Blood draws for most people do not cause any serious problems. However, they may cause minor discomfort, bleeding, bruising, soreness or infections at the site on rare occasions. There may be some discomfort when the intravenous line is placed in the vein and there may be some bruising and soreness afterwards. There are no known medical risks associated with iv injection of small amounts of deuterated glucose, insulin, glucagon, somatostatin and growth hormone for the duration of the clamp. All of these substances are washed out of the system after the infusion is stopped and there are no lasting effects.

There are no known lasting effects associated with MRI scanning. Participants may perceive minor discomfort due to the scanner sounds. They will be provided with earplugs to minimize discomfort. Participants will be screened thoroughly to ensure that there are no metallic objects or implants on them.

Some of the assessments, in particular, the questionnaires, may be upsetting to study participants. We will minimize all of these by having all assessments performed by well-trained research staff with clinical experience and appropriate skills to maximize the participants’ comfort and keep their distress to a minimum during each visit.

Olanzapine is approved for the treatment of psychotic illness. It can cause side effects such as fatigue/sleepiness (26%), headache (17%), dry mouth (7%), constipation (9%), and muscle side effects. Muscle side effects may occur, and include restlessness (23%), decreased movements (<5%), muscle stiffness and rigidity (<5%) or abnormal posture of neck or hand due to muscle rigidity, called dystonia (<5%). If any of these side effects occur, they will be assessed and treated promptly.

In humans, with acute administration of intranasal insulin, no adverse effects have been reported. Moreover, in more chronic studies, 8 weeks of intranasal administration of intranasal insulin at a dose of 40 IU QID (total daily dose 160 IU) did not cause any adverse effects.

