In general, placebo medication does not cause any side effects. All these side effects are temporary and will disappear (if they occur) within 24 hours of the last dose. A physician will be available at all times during the study to promptly assess and treat any side effects. A staff will always be available in evenings and overnight during the period that participants are taking study placebo/drug and not in hospital. Participants will be provided with an emergency contact card. This card will have contact information listed for study staff who will be able to contact the participant within 20 minutes of a call. In the advent of an unexpected emergency, participants are also advised they can call 911.

Hypoglycemia as a result of intranasal insulin has not been found to be a concern in the literature and across healthy volunteers there have been no reports of hypoglycemia as a result of an intranasal insulin dose equal or higher to what will be used in this protocol. In the metabolic protocol, glucose is monitored as part of the euglycemic clamp procedure and euglycemia is maintained through a peripheral glucose infusion. In the cognitive protocol, we will closely monitor for signs and symptoms of hypoglycemia, including shakiness, confusion, increased heart rate, lightheadedness, impaired vision, headaches, and weakness. In the event that any of these should occur, there will be a glucose metre and lancet in the testing room to measure glucose. If the level is below 2.8mmol/L, the study will be stopped and juice and/or glucose will be administered as deemed necessary by PI or PI designate.

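### The clamp's basal insulin is printed as 0.05 units/kg/min, 300 times the protocol's own spillover-matching dose over the same 30 minutes, so the printed rate cannot be basal

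*Protocol*

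**What the plan says.** The clamp is set out in the protocol under Study Design and Assessments, Pancreatic euglycemic clamp, Day 2. Somatostatin starts at t = -120 min to suppress insulin, glucagon and growth hormone, which are "concurrently replaced by a basal rate infusion of these hormones". The insulin component is "insulin (Humulin R, Eli Lilly Canada) at 0.05units/kg/min". The clamp lasts 480 minutes in total.

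At t = 0 "the participants receive 40 IU of intranasal insulin (INI) lispro", or intranasal placebo. Because some of the nasal dose reaches the circulation, "volunteers during the INP visit will receive an IV infusion of insulin lispro 0.005IU/kg" over 30 minutes, and the diluent is infused instead at the intranasal-insulin visits.

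Two other places bear on how large the background infusion is meant to be:

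- Background/Rationale, part iv, describes the rat clamp on which the human study is modelled and explains why the hyperinsulinemic clamp was avoided: "The HIEC involves a high dose of intravenously infused insulin which continuously reaches the brain", "making dissection of peripheral and central effects difficult". Basal replacement is given there as the way round this.
- Risks/Benefits states: "There are no known medical risks associated with iv injection of small amounts of deuterated glucose, insulin, glucagon" and the other clamp hormones.

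**The concern.** Two insulin doses in the same procedure do not fit together. One is called basal. The other is a small correction, considered large enough to need matching between visits. If the basal figure is right, the correction is negligible. If the correction matters, the basal figure is far too large.

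Two things are at stake. The first is safety: this is an operative intravenous insulin dose for healthy volunteers as young as 17, given at every metabolic visit (27 complete data sets × 3 clamps = 81 infusions). The second is the primary outcome. If the printed rate were infused, every visit would take place under the high-insulin condition that the protocol says it avoids. Endogenous glucose production could then be suppressed at all visits, masking the contrast between intranasal insulin and placebo, and the intended separation of central from peripheral insulin action would be lost.

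**Working it through.** **Inputs.** From the Day 2 clamp steps: background insulin 0.05 units/kg/min; spillover-matching dose 0.005 IU/kg in total over 30 min; nasal dose 40 IU; 120 min of infusion before t = 0; 480 min overall. Body weight is not given. I assume 70 kg with a range of 50 to 90 kg, and only the absolute totals depend on it. The protocol shows no derivation of the rate, so there is no calculation of its own to reproduce.

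**Background against matching dose, same 30 minutes**

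- Background: 0.05 × 30 = 1.5 units/kg
- Ratio: 1.5 / 0.005 = 300, independent of weight
- Matching dose as a share of background: 0.005 / 1.5 = 0.33%
- Time for the background to deliver the whole matching dose: 0.005 / 0.05 = 0.1 min = 6 seconds

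**Totals at the printed rate**

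| | per kg | 50 kg | 70 kg | 90 kg |
| --- | --- | --- | --- | --- |
| Before t = 0 (0.05 × 120) | 6 units | 300 | 420 | 540 |
| Whole clamp (0.05 × 480) | 24 units | 1,200 | 1,680 | 2,160 |
| Pre-dose total / 40 IU | – | 7.5 | 10.5 | 13.5 |
| Minutes to reach 40 units, 40 / (0.05 × weight) | – | 16.0 | 11.4 | 8.9 |

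The background would exceed the entire nasal dose within roughly 9 to 16 minutes.

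**Which unit would reconcile the figures?**

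- Milliunits: 0.05 × 30 = 1.5 mU/kg against a matching dose of 5 mU/kg. The match is then 5 / 1.5 = 3.3 times background, a correction worth making. At 70 kg the infusion would be 0.05 × 70 × 60 = 210 mU/h, or 0.21 units/h, and 1.68 units over the clamp.
- Microunits: 0.05 × 30 = 1.5 µU/kg against 5,000 µU/kg, a mismatch of about 3,300-fold in the other direction. A lost micro sign therefore does not resolve the conflict.

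**The case against.** The strongest case on the other side has five parts.

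1. *It may be a text-conversion slip.* A prefix dropped before a spelled-out unit would leave exactly this text. That cannot be fully excluded, but the micro sign survives in the somatostatin rate in the same bullet, and a lost micro sign would not reconcile the doses anyway. The clamp figure is also not visible here and may carry infusion rates, so the absence of a correction can be asserted only for the readable text.

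2. *The effect on the primary contrast needs careful wording.* The same background runs at every visit. Against so large a background, unmatched spillover would hardly alter peripheral insulin, so the high rate would not bias the contrast through spillover. This is right. The plausible harm is masking, together with loss of the basal state on which the central interpretation depends, and it arises only if the printed rate is infused.

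3. *Basal is never defined numerically, the warning about high-dose insulin describes rats, and small amounts has no number attached.* All true. That the rate cannot be basal is therefore an inference. It rests mainly on the two human doses, and the protocol itself calls the human work analogous to the rodent model. Comparing regular insulin with lispro unit for unit does not disturb a 300-fold gap.

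4. *Milliunits are not proven either.* During the matching infusion the placebo visit would receive (1.5 + 5) / 1.5 = 4.3 times background. The document cannot confirm 0.05 mU/kg/min as the intended value, so the source record must decide.

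5. *Safeguards exist and a misprint leaves the design intact.* Dextrose is titrated, a physician is available, and "glucose is monitored as part of the euglycemic clamp procedure and euglycemia is maintained through a peripheral glucose infusion". These measures reduce the hypoglycemia risk but do not make the rate basal, and the remaining hypoglycemia text addresses intranasal insulin rather than a large intravenous dose. A likely unit error in an insulin order still needs correcting before anyone relies on it.

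**Conclusion.** The point holds: the insulin rate is wrong as written. It is 300 times the matching dose over the same 30 minutes at any body weight, and it totals 24 units/kg over the clamp (1,680 units at an assumed 70 kg, 1,200 to 2,160 over 50 to 90 kg). That cannot be squared with a basal label, with a spillover match worth making, or with the stated wish to avoid high-dose intravenous insulin.

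Confidence in the inconsistency is high. Confidence in the cause is lower: a unit misprint, probably of 1,000-fold, is the likeliest reading, but the intended unit is not stated in the document. Nothing shows that the printed rate was or will be infused, so the consequences for the primary outcome and for safety are conditional on that. The correction is nevertheless essential, because this line governs the dose.

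**What to change.** - Check the insulin rate against the pharmacy order or infusion worksheet, and correct the figure or unit in the Day 2 clamp steps. Milliunits per kg per minute is the candidate to test, not a value to insert unchecked.
- If any clamps have been run, confirm the rate actually given from the infusion records and from the plasma insulin results the protocol already collects.
- In the same correction, confirm the unit of the deuterated glucose tracer. As read it is in mmol: 22.5 + 0.25 × 480 = 142.5 mmol/kg, about 1.8 kg at 70 kg (1.3 to 2.3 kg over 50 to 90 kg) with an assumed molar mass of about 182 g/mol. In µmol it would be about 1.8 g. This is a low-confidence side check. The prefix may be a conversion slip, there is no second figure to test it against, and the insulin finding does not depend on it.

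The cost is a one-line dose correction in an amendment to the ethics board and a pharmacy cross-check, plus a look at past infusion records if there are any. Design, visits and sample size are unaffected.

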**Participants**

Healthy non-obese volunteers (age 17-45) will be recruited through approved postings at our academic centres for the metabolic arm. This is a proof-of-concept study, based largely on work by [name], examining males(31). Central insulin has sex-dependent effects in relation to appetite/food palatability(32). Sex-dependency, to our knowledge, not yet been assessed in relation to glucose metabolism while the cognitive effects on insulin have been demonstrated in both sexes (33). We will examine both sexes and investigate the effect of sex on the outcomes of interest.

Participants will be enrolled to reach complete data sets of n=27 and n=32 in the metabolic and cognitive arms of the study respectively. Therefore, participants who drop out or who are withdrawn will be replaced.

**Selection Criteria**

Inclusion Criteria – All participants

Participants of any race or ethnicity meeting all criteria listed below will be included in the study:

# Ages 17-45

Exclusion Criteria – All Participants

1. History of psychiatric illness (the Mini International Neuropsychiatric Interview (MINI) will be used to screen for psychiatric illness in the present or past Participants will be excluded for moderate to severe substance use.
2. Left handedness (only for the cognitive and MRI arm)
3. Pre-diabetes or diabetes (fasting glucose ≥6.0mmol/L or use of anti-diabetic drug);
4. Evidence of impaired glucose tolerance on screening OGTT;
5. Family history of diabetes (first degree relative such as a parent or sibling);
6. Use of weight reducing agents or other medications based on the discretion of the PI;
7. History of liver disease or AST> 2 times upper limit of normal;
8. History of kidney disease;
9. Major medical or surgical event within the last 6 months
10. Any condition that interferes with safe acquisition of MRI data such as metal implants, pacemakers, cochlear implants, claustrophobia, etc. (only for the cognitive and MRI component)
11. Pregnancy and/or breastfeeding

**Termination of the Study**

Reasons for withdrawing individual participants from the study may include one or more of the following:

1. Major protocol violation
2. Participant lost to follow-up
3. Withdrawal of consent
4. Participant pregnant or breast-feeding

Any participant may be discontinued from the study at the discretion of the investigators if this is deemed to be in the best interest of the participant. The decision may be made either to protect the participant’s health and safety, or because it is part of the research plan that people who develop certain conditions may not continue to participate.

Any research information recorded for, or resulting from, participation in this research study prior to the date that the subject formally withdrew their consent will be retained and may continue to be used and disclosed by the investigators for research purposes; however, no new data will be collected.

1. **Data Analysis Plan and Power Calculation**

Power Analysis: Using data from [name] previous study also employing a randomized cross-over design^32^, we found that a sample of 16 subjects would be needed to detect a 20% difference between INI-PL relative to INP-PL in endogenous glucose production, with 80% power to detect an effect size Cohen’s d = 0.66. We used a conservative estimate of the correlation between period 1 and period 2 (= 0.2). To account for the three comparisons among the three groups in the metabolic arm (using Bonferroni adjustments for multiple tests) and based on an expected attrition rate of 20% and the need to keep the total number of participants as a multiple of 3 (to counterbalance the order effects of the four treatment periods), we will recruit 27 participants to the metabolic arm of the study. To account for the six comparisons among the four groups in the cognitive arm of the study, we will recruit 32 participants to this arm. As the cognitive portion of the study is exploratory, data will be used to generate future sample sizes. The fMRI data will be analyzed using SPM12. Contrasts will be generated for activation differences between task conditions. ASL and resting state fMRI data will be analyzed using appropriate tools available in SPM12 and FSL libraries. MRS data will be analyzed using LCModel to quantify glutamate content in the VOI. Data across modalities will be analyzed in a repeated measures ANOVA design to investigate the effect of treatments. These analyses will be conducted by SMA under the supervision of AGG and AV.

To address our primary hypothesis, which is the comparison within subject between treatments, Mixed Effect Models will be used. The four treatments, time, and sequences will be entered as predictors and subject will be used as clusters in a random intercept model. In addition to examining outcome measures within subjects across treatments, predictors accounting for order effects will be included in the analyses. Mixed Effect Models will be adjusted with SAS System 9.4. A similar approach is used for cognitive data, where measures of sedation will be used as covariates.

1. **Risks/Benefits**

Blood draws for most people do not cause any serious problems. However, they may cause minor discomfort, bleeding, bruising, soreness or infections at the site on rare occasions. There may be some discomfort when the intravenous line is placed in the vein and there may be some bruising and soreness afterwards. There are no known medical risks associated with iv injection of small amounts of deuterated glucose, insulin, glucagon, somatostatin and growth hormone for the duration of the clamp. All of these substances are washed out of the system after the infusion is stopped and there are no lasting effects.

There are no known lasting effects associated with MRI scanning. Participants may perceive minor discomfort due to the scanner sounds. They will be provided with earplugs to minimize discomfort. Participants will be screened thoroughly to ensure that there are no metallic objects or implants on them.

Some of the assessments, in particular, the questionnaires, may be upsetting to study participants. We will minimize all of these by having all assessments performed by well-trained research staff with clinical experience and appropriate skills to maximize the participants’ comfort and keep their distress to a minimum during each visit.

Olanzapine is approved for the treatment of psychotic illness. It can cause side effects such as fatigue/sleepiness (26%), headache (17%), dry mouth (7%), constipation (9%), and muscle side effects. Muscle side effects may occur, and include restlessness (23%), decreased movements (<5%), muscle stiffness and rigidity (<5%) or abnormal posture of neck or hand due to muscle rigidity, called dystonia (<5%). If any of these side effects occur, they will be assessed and treated promptly.

In humans, with acute administration of intranasal insulin, no adverse effects have been reported. Moreover, in more chronic studies, 8 weeks of intranasal administration of intranasal insulin at a dose of 40 IU QID (total daily dose 160 IU) did not cause any adverse effects.

In general, placebo medication does not cause any side effects. All these side effects are temporary and will disappear (if they occur) within 24 hours of the last dose. A physician will be available at all times during the study to promptly assess and treat any side effects. A staff will always be available in evenings and overnight during the period that participants are taking study placebo/drug and not in hospital. Participants will be provided with an emergency contact card. This card will have contact information listed for study staff who will be able to contact the participant within 20 minutes of a call. In the advent of an unexpected emergency, participants are also advised they can call 911.

Hypoglycemia as a result of intranasal insulin has not been found to be a concern in the literature and across healthy volunteers there have been no reports of hypoglycemia as a result of an intranasal insulin dose equal or higher to what will be used in this protocol. In the metabolic protocol, glucose is monitored as part of the euglycemic clamp procedure and euglycemia is maintained through a peripheral glucose infusion. In the cognitive protocol, we will closely monitor for signs and symptoms of hypoglycemia, including shakiness, confusion, increased heart rate, lightheadedness, impaired vision, headaches, and weakness. In the event that any of these should occur, there will be a glucose metre and lancet in the testing room to measure glucose. If the level is below 2.8mmol/L, the study will be stopped and juice and/or glucose will be administered as deemed necessary by PI or PI designate.

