**1.2 Hypotheses**

1. Primary hypothesis (Glucose metabolism: Pancreatic euglycemic clamp experiments):

Intranasal insulin (INI) will be associated with a decrease in **endogenous** **glucose production** (EGP) (our primary outcome measure) relative to intranasal placebo (INP). This effect of glucose production lowering by INI will be lost if OLA is co-administered. In the absence of INI administration, there will be no difference between OLA and oral placebo (PL). We do not expect any of the treatments to differ with respect to glucose disposal (Gd). Predicted differences between treatments in Dextrose Infusion Rate (InfR) reflect differences in EGP. In summary, we predict the following treatment effects **relative to the INP-PL group** (i.e. no active treatment) (Table 1):

| Treatments | | Measures derived from Pancreatic clamp procedure | | |
| --- | --- | --- | --- | --- |
| Intranasal | Oral | Dextrose InfR | EGP | Gd |
| INI | PL | 🡹 | 🡻 | 🡺🡸 |
| INI | OLA | 🡺🡸 | 🡺🡸 | 🡺🡸 |

1. Secondary hypothesis (Cognition):

OLA will be associated with decrements in cognitive measures as compared to PL. Further, OLA will block the beneficial effect of INI on cognition. Hence, there will be no difference between the INI and INP in the presence of OLA (and performance in both these arms will be worse than that in the INP-PL arm). In summary, we predict the following treatment effects **relative to the INP-PL group** (Table 2):

| Treatments | | Cognition:  (visuospatial memory and verbal memory) |
| --- | --- | --- |
| Intranasal | Oral |  |
| INI | PL | 🡹 |
| INP | OLA | 🡻 |
| INI | OLA | 🡻 |

- 1. We also hypothesize that INI will result in adaptive changes in neurochemical and neurohemodynamic measures as studied using MRI techniques. Furthermore, OLA will block these effects of INI.

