**Figure 3: Preliminary data** Olanzapine (OLA) abolishes suppression of hepatic glucose production by central insulin (INS), measured using pancreatic euglycemic clamps in Sprague-Dawley rats. Graph shows suppression hepatic glucose production (%) during steady state clamp relative to basal. p<0.05 all groups vs. INS-Vehicle (VEH). There was no effect of OLA on the rate of glucose disposal (data not shown).

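### The primary model omits the pre-dose EGP obtainable at every clamp visit, which costs some precision for INI-PL versus INP-PL; adding it is a cheap, optional gain

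*Protocol*

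**What the plan says.** **Timing (Protocol, Pancreatic euglycemic clamp, Day 2).** The clamp begins two hours before dosing: "t=-120 minutes), the pancreatic euglycemic clamp (total duration 480 minutes) will be initiated". On the tracer: "Glucose production is quantified via a primed constant infusion of D2-glucose (dextrose infusion"), and it is "administered for the duration of the clamps". On sampling: "Blood samples are drawn every 30 min after the start of the clamp (t=-120 min to t=0 min), and every 10 minutes after intranasal insulin". The intranasal dose and the day-2 oral dose are both given at t=0.

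**Oral treatment before the clamp (Study Design and Assessments).** Olanzapine or placebo is also taken on the evenings of days 0 and 1. At INI-PL and INP-PL visits it is placebo throughout; at the INI-OLA visit it is olanzapine.

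**Endpoint (1.2 Hypotheses).** "Intranasal insulin (INI) will be associated with a decrease in" EGP, the primary outcome. The text does not say whether EGP is analysed as a level, a change or a percentage of the pre-dose value.

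**Model (Data Analysis Plan and Power Calculation).** "The four treatments, time, and sequences will be entered as predictors and subject will be used as clusters in a random intercept model". The next sentence adds predictors for order effects. Covariates are named only for the cognitive data (sedation). The mention of four treatments does not fit the three-treatment metabolic arm; that is a separate matter.

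**Sizing (same section).** 16 subjects for INI-PL versus INP-PL at 80% power and d = 0.66, raised to 27 for three Bonferroni-adjusted comparisons and 20% attrition. "We used a conservative estimate of the correlation between period 1 and period 2 (= 0.2").

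**The concern.** A subject random intercept removes only what is stable across a participant's visits. On the planning correlation of 0.2, that is a minor share of the variance; the rest, 1 − 0.2 = 0.8, varies between visits within a person. Part of it is the participant's metabolic state that day, and the pre-dose EGP measures the outcome itself on the same day under the same clamp. The model lists its terms and this value is not among them, so whatever it could explain stays in the error of the INI-PL versus INP-PL contrast.

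That contrast is the one the trial is sized on. The olanzapine question is whether the insulin effect disappears, so it can be answered only if the insulin effect is first shown. Avoidable noise there raises the chance that the trial is uninformative.

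**Working it through.** **Inputs from the Protocol:** n = 16 and 27, d = 0.66, between-period correlation r = 0.2, three Bonferroni comparisons. **Assumed:** two-sided testing at 0.05/3 = 0.0167, since neither alpha nor sidedness is stated; and rho, the correlation between the pre-dose and post-dose differences of the two visits, ranged from 0 to 0.7.

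**1. Reproduce n = 16.** For a paired t-test the noncentrality is dz·√n on n − 1 df. With 0.66 read as the paired effect dz, 0.66 × √16 = 2.64. A one-sided 5% test then has 80.9% power, and 16 is the smallest n that reaches 80%. A two-sided 5% test has 69.4% and needs 21. If 0.66 is on the raw SD, dz = 0.66/√(2 × (1 − 0.2)) = 0.522, and the need is 25 (one-sided) or 31 (two-sided). Only the paired reading, one-sided, returns the Protocol's figure.

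**2. Unadjusted power at n = 27.** With dz = 0.66, the noncentrality is 0.66 × √27 = 3.43; at two-sided 0.0167 power is 80.1%. With dz = 0.522 it is 56.7%.

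**3. Adjust for pre-dose EGP.** The contrast variance is multiplied by 1 − rho², so dz becomes dz/√(1 − rho²), with one df lost. At rho = 0.5: 0.66/√0.75 = 0.762.

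| rho (assumed) | variance factor | dz=0.66, n=27 | dz=0.66, n=21 | dz=0.522, n=27 |
|---|---|---|---|---|
| unadjusted | – | 80.1% | 66.0% | 56.7% |
| 0 | 1.00 | 79.9% | 65.6% | 56.4% |
| 0.2 | 0.96 | 81.7% | 67.7% | 58.5% |
| 0.3 | 0.91 | 83.9% | 70.4% | 61.2% |
| 0.5 | 0.75 | 90.9% | 79.7% | 71.1% |
| 0.7 | 0.51 | 98.3% | 93.5% | 88.1% |

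The n = 21 column applies if 27 are recruited and 20% are lost (27 × 0.8 = 21.6). The Participants section instead promises 27 complete data sets with replacement, so n = 27 is the main case. At rho = 0.5 the confidence interval is narrower by 1 − √0.75 = 13%; at rho = 0.3 by 1 − √0.91 = 5%.

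**4. Would a change score do instead?** If pre-dose and post-dose differences have equal variance (assumed), analysing change from pre-dose multiplies the variance by 2(1 − rho): 1.6 at rho = 0.2, 1.4 at 0.3, 1.0 at 0.5 and 0.6 at 0.7. Below rho = 0.5 this is worse than no adjustment, and at each of these values it is worse than the covariate.

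**5. Can all three contrasts be adjusted?** In simulation, a 0.5 SD olanzapine shift in pre-dose EGP that does not carry into the post-dose value moved the adjusted INI-OLA estimate by about 0.14, 0.24 and 0.35 SD at rho = 0.3, 0.5 and 0.7. Unrestricted adjustment could therefore introduce a bias that the present model does not have.

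**The case against.** **The endpoint may already use the baseline.** EGP is not defined as level or change, and the group's rat data were shown against a reference: "Graph shows suppression hepatic glucose production (%) during steady state clamp relative to basal". An SAP, not seen here, might define the endpoint that way or add the covariate. This stands as a caution, and either would narrow the point or settle it. But the Protocol goes beyond silence: it lists the model's terms. Figure 3 does not define basal as a pre-dose value within the clamp, so it gives little support to either side.

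**The trial is not short of power because of this.** A reader might take 56.7% as the true starting point. That reading of d does not reproduce n = 16. On the reading that does, 27 complete data sets give 80.1% without adjustment, so the covariate is a bonus rather than a repair. This stands.

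**Rho is unknown, and r = 0.2 limits little.** The Protocol calls 0.2 conservative, and the remaining 80% includes measurement error and subject-by-treatment variation that a pre-dose value cannot remove. Nor is pre-dose EGP the sole same-day information: hormones, free fatty acids, diet and activity are also recorded. All of this stands.

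**Pre-dose quality.** Tracer, somatostatin and hormone replacement all start at t=-120, so early samples fall in the run-in. This also undercuts a further inference, that pre-dose samples dilute the treatment effect if time means time within the clamp. The Protocol does not say that pre-dose draws enter as outcomes, and no tracer-based EGP exists at the moment the tracer starts.

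**Limited reach.** Only one of three contrasts benefits, and mixing adjusted and unadjusted contrasts complicates joint reading. This stands, and is why the point is optional.

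**Conclusion.** The point holds as an efficiency suggestion for INI-PL versus INP-PL. A pre-dose value unaffected by treatment is obtainable at both visits at no extra cost, and the stated model does not use it. The loss is one of precision: nothing in the Protocol supports reading it as bias, as a failed sample size, or as a flaw in the olanzapine contrasts.

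On the paired reading with 27 completers and two-sided 0.05/3, the gain is about 2 points of power at rho = 0.2, 4 at 0.3, 11 at 0.5 and 18 at 0.7, against a cost of about 0.2 points at rho = 0. It is therefore negligible below about 0.2 and worthwhile from roughly 0.3 to 0.5 upward. These figures rest on the assumed rho, alpha and sidedness. An optional, cheap improvement.

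**What to change.** State in the analysis section that the primary EGP analysis uses values after t=0. For INI-PL versus INP-PL, add two covariates: that visit's pre-dose EGP (mean of the last samples up to t=0, after tracer run-in) and the participant's mean pre-dose EGP over the two oral-placebo visits, so that the adjustment works within subject. Name the samples in advance.

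Keep contrasts involving INI-OLA unadjusted as primary and show adjusted versions as supportive only. If EGP is meant as change or percentage from pre-dose, say so and still include the pre-dose value as a covariate for INI-PL versus INP-PL.

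Cost: a short addition to the plan and one or two degrees of freedom, with no new samples or visits. Each reported contrast must be labelled as adjusted or unadjusted, because the three estimates need no longer add up exactly.
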